### Data collection and management

2.7

#### Plans for assessment and collection of outcomes

2.7.1

The variables of interest are assessed via digital self-assessment questionnaires via the online platform Unipark (Tivian XI GmbH, Cologne, Germany).

#### Plans to promote participant retention and complete follow-up

2.7.2

Participants are free to withdraw from the study at any time, and without providing a reason. In such cases, no further outcome data will be collected. To encourage completion of the six-month follow-up assessment, participants will receive reminder emails one and two weeks after receiving the initial invitation to complete the follow-up questionnaire. If the questionnaire remains incomplete after three weeks, a final reminder will be issued via telephone.

#### Data management

2.7.3

As data collection is conducted digitally via Unipark, information is entered directly by participants, therapists and research assistants. The data is then exported from the platform’s database in CSV or SPSS format.

#### Confidentiality

2.7.4

Participant data is collected in pseudonymized form. For statistical evaluation, the data is transferred to the analysis software R and SPSS. Access to the keys that link pseudonyms to individual identities, as well as to the digitally recorded health-related participant data, is restricted exclusively to authorized study personnel at the respective rehabilitation clinics.

### Statistical methods

2.8

#### Statistical methods for primary and secondary outcomes

2.8.1

Demographic data will be used to describe study participants and reported as means and standard deviations or median and interquartile range, where appropriate. The change in primary and secondary outcomes as well as objective measures from the beginning to the end of rehabilitation for each intervention group individually with the control group will be analyzed with 2x2 ANOVAs (2 time points x 2 groups). The longterm effects after six months will also be analyzed for each intervention group with separate 3x2 ANOVAs (3 time points x 2 groups). Since this is the first study involving these interventions in patients with PCS, prior correction will not be used, but will be discussed appropriately in the publication of the results. For the exploratory evaluation of personality measures, we plan to calculate predictor analyses, such as regression analyses to predict changes in primary and secondary outcomes.

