### Design

2.3

The multicenter, longitudinal, quantitative trial employs a quasi-experimental, non-randomized sequential cohort design with three arms in a real-life design. The entire project will run from January 01, 2024, until expected June 30, 2027.

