#### Explanation for the choice of comparators

2.5.1

Throughout the study, all three study groups participate in regular psychosomatic rehabilitation and receive treatment as usual (TAU) in accordance with the guidelines of the German pension insurance for patients with PCS. The control group (group 1) receives only TAU, while the other two groups additionally receive one of the two interventions (group 2 = JOURNAL group; group 3 = FRAME group). Although participants are assigned to groups according to a sequential cohort design, systematic differences or changes in symptom burden should be minimal and attributed to group affiliation and whether a study intervention was received. Which group participants are in depends solely on the timing of their rehabilitation, not on other systematic differences. (see **Figure 1**). Patients are informed about the study on the first day in the rehabilitation hospital. All treating providers are aware of the participants’ condition assignments.

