#### Sample size

2.5.9

A total sample of N = 84 participants will participate in one of three groups: a control group receiving treatment as usual only (TAU), a JOURNAL group, and a FRAME group, with 28 individuals in each group. Case numbers are based on the following facts: In general, hardly any studies have been published on the effectiveness of psychosomatic rehabilitation measures for patients with PCS (42). Initial studies show medium to large effects, depending on the outcome variable. For example, effects were observed for somatoform complaints (d=0.60) and the 6-min walking test (d=1.22) (6). No study could be found that showed effect sizes for changes in earning capacity or ability to work. Rief et al. (26) found a large effect size (approximately d=1.0, calculated from the data in the article) for improvements in limitations and the subjective assessment of ability to work in hours (approximately d=2.0, calculated from the data in the article) through the intervention to optimize expectations in patients undergoing bypass surgery. As the patients in this study are already undergoing psychosomatic rehabilitation treatment, the intervention is an add-on that may not show a statistically large effect (Cohen’s d > 0.8). Therefore, the sample size should be large enough to detect a medium effect. Furthermore, it should be possible to test the effectiveness of each intervention compared to the treatment as usual (TAU) group. For a 2x2 analysis of variance with repeated measures (ANOVA; 2 groups x 2 time points) for the change in the main outcome measure (e.g., WAI) from admission to discharge, with a mean effect size of f=0.25 and a power of 0.95, N = 54 patients are required for the comparison of TAU with one of the intervention groups (calculated with G*Power 3.1.9.6; freeware from Kiel University). In order to compare the second intervention group with the TAU group, further N = 54/2 = 27 patients are required in this group. In total, this equates to N = 81 patients. To be able to divide these patients between the two clinics and the three groups, a total of N = 84 patients are required, for whom at least admission and discharge data are available. This means that the sample is also sufficiently large for 2x3 ANOVAs (2 groups x 3 time points; N = 36 required). In summary, we plan to conduct two 2×2 ANOVAs, specifically using a mixed-design ANOVA (two-factor ANOVA with one repeated-measures factor and one between-group factor). With an estimated drop-out rate of 20%, 100 patients must be recruited.

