### Assignment of interventions: sequential cohort design

2.6

In order to recruit enough patients within a reasonable timeframe, the study will be conducted at two locations. Due to different treatment concepts at each rehabilitation clinic, this will also increase the study’s external validity. Patients will be recruited into the two intervention groups and the control group in clusters, with a wash-out phase in each clinic. This means that only one group will be recruited and examined at a time, and the next group will only be recruited two weeks after the previous group has been fully discharged. This reduces confounding factors, such as disappointed patients in the control group talking to patients in an intervention group. The random allocation of patients is based on their start date on the rehabilitation program.

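### The primary analysis is an unadjusted comparison of WAI change; adjusting for T1 WAI, clinic and a few covariates would gain precision, but calendar-period confounding would remain and should be stated

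*Protocol article*

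**What the plan says.** Section 2.8.1 of the protocol article states that change in primary and secondary outcomes "for each intervention group individually with the control group will be analyzed with 2x2 ANOVAs (2 time points x 2 groups". Section 2.5.9 repeats the choice, "In summary, we plan to conduct two 2×2 ANOVAs", and names the only factors: "two-factor ANOVA with one repeated-measures factor and one between-group factor". The model is therefore specified in the article; it is not a detail left open for an analysis plan. Demographic variables are mentioned in 2.8.1 only for describing the sample.

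On design, section 2.3 describes a "quasi-experimental, non-randomized sequential cohort design with three arms in a real-life design". Section 2.5.1 argues that "Which group participants are in depends solely on the timing of their rehabilitation, not on other systematic differences", while section 2.5.3 concedes that selection bias is possible. Section 2.6 says of the two sites: "Due to different treatment concepts at each rehabilitation clinic, this will also increase the study’s external validity". Each clinic recruits one group at a time (2.5.10, 2.6). Recruitment runs until 14 patients per group and clinic meet the adherence criterion (2.8.2), with 42 patients per site (2.9.1).

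WAI and PHQ-9 are measured at T1 (2.5.7), and age, sex and employment are recorded (2.4).

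**The concern.** The group-by-time test of a 2x2 mixed ANOVA is algebraically a t-test on the T2 minus T1 difference. It uses T1 WAI but does not estimate how strongly T1 predicts T2. It leaves any clinic difference in change in the error term and makes no use of the patient characteristics collected at admission.

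In a small non-randomised comparison with 28 patients per group, admission differences between cohorts are to be expected, by chance if for no other reason. At stake is precision, together with the ability to show that a result does not rest on measured differences in case mix. The data needed for a better model are already being collected.

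**Working it through.** **Inputs.** From section 2.5.9: f = 0.25, power 0.95, N = 54 per pairwise comparison, 28 per group in the final sample. Not stated and therefore assumed: two-sided alpha 0.05, and the T1–T2 correlation rho of the WAI (0.5, range 0.3 to 0.8).

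**1. Reproducing the plan's figure.** For the group-by-time interaction with k = 2 groups and m = 2 times, lambda = f² × N × m/(1 − rho) = 0.0625 × 54 × 2/0.5 = 13.5 on 1 and 52 df. Power is 0.9501, so N = 54 is reproduced at rho = 0.5. In a 2x2 layout f = 0.25 means a between-group difference in change of 4 × 0.25 = 1.0 raw SD. As a check, 1.0²/(2/27) = 13.5.

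**2. Precision.** In units of the raw variance, the residual variance is 2(1 − rho) for change and 1 − rho² with an estimated T1 slope. The ratio is (1 − rho²)/[2(1 − rho)] = (1 + rho)/2. The table compares the change score with a pairwise model containing T1 WAI and clinic. Each pair of figures reads change → adjusted.

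| rho | Variance | Ratio | N per pair for power 0.95, 1.0 SD effect | Power at 28 per group, 1.0 SD | Power at 28 per group, 0.5 SD (assumed effect) |
|---|---|---|---|---|---|
| 0.3 | 1.40 → 0.91 | 0.65 | 76 → 50 | 0.874 → 0.971 | 0.342 → 0.486 |
| 0.5 | 1.00 → 0.75 | 0.75 | 54 → 42 | 0.957 → 0.989 | 0.451 → 0.564 |
| 0.7 | 0.60 → 0.51 | 0.85 | 34 → 30 | 0.997 → 0.999 | 0.660 → 0.729 |
| 0.8 | 0.40 → 0.36 | 0.90 | 24 → 22 | 1.000 → 1.000 | 0.828 → 0.864 |

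The two extra terms move the critical t from 2.005 (54 df) to 2.007 (52 df). A model over all 84 patients with three group means, T1 WAI and clinic would have 84 − 5 = 79 residual df. Any further gain from age, sex, employment or PHQ-9 is not counted, because the article gives no figure for it.

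**3. Clinic.** With equal cells, a clinic gap of g SD in change adds g²/4 to the residual variance of an unadjusted analysis. At rho = 0.5 and a 1.0 SD effect, power without a clinic term is 0.957, 0.955, 0.946 and 0.927 for g = 0, 0.2, 0.5 and 0.8, against 0.957 with the term. The loss is small unless the clinics differ a lot.

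**4. Bias.** Simulation with a true effect of zero, 28 per group, 14 per clinic, rho = 0.5 and 6,000 runs per scenario. The adjusted model contains T1 WAI and clinic.

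| Scenario | Change score: mean estimate (rejection rate) | Adjusted: mean estimate (rejection rate) |
|---|---|---|
| No systematic imbalance | 0.000 (0.042) | −0.001 (0.049) |
| Stable 0.5 SD cohort difference | −0.005 (0.043) | +0.247 (0.172) |
| 0.5 SD difference at T1 only | −0.502 (0.425) | −0.252 (0.174) |
| 0.3 SD calendar shift at T2 | +0.298 (0.176) | +0.300 (0.242) |

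Algebra agrees. A stable difference D biases the adjusted estimate by (1 − rho)D = 0.25. A T1-only difference biases change by −D = −0.50 and the adjusted estimate by −rho × D = −0.25. Without systematic imbalance the simulated standard errors are 0.267 for change and 0.234 for the adjusted estimate.

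**The case against.** A change-score ANOVA is a recognised and valid analysis of the hypotheses in section 1, which concern improvement from before to after treatment. The article also presents itself as preliminary work that a randomised trial should follow (3.1). That stands, and it limits how serious the point is. It does not decide between the models, because regressing change on group and T1 WAI gives the same group estimate as regressing T2 WAI on them.

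Four stronger readings are tempting, and the documents do not support them.

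- A reader might infer that baseline WAI is ignored. It is one of the two time points; what is missing is an estimated slope.
- A reader might infer that leaving out clinic confounds the comparison. The quota of 14 per group and clinic balances clinic by design, so the cost is precision. One reservation remains: section 2.8.2 does not say whether non-adherent patients are analysed. If they are, the cells could be unequal.
- A reader might count chance imbalance as a separate harm. With 28 per group the SE of the T1 difference is √(2/28) = 0.267 SD, and a gap of that size shifts the change estimate by (1 − 0.5) × 0.267 = 0.13 SD. That is the precision loss again: √(0.0714 − 0.0536) = 0.13.
- A reader might infer that adjustment removes bias at no cost. If section 2.5.1 is right that only timing determines group, both estimators are unbiased on average. If it is wrong, the answer depends on whether cohort differences are stable or transient. In the stable case the adjusted model is the biased one.

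**Conclusion.** The point holds as an improvement that should be made; it does not make the planned analysis invalid. The article fixes a two-factor model without an estimated T1 slope, a clinic term or covariates, in a design where all three are available and relevant. Adjustment lowers residual variance by 25% at rho = 0.5 (35% at 0.3, 10% at 0.8). Power at 28 per group rises from 0.957 to 0.989 for the plan's implied 1.0 SD effect. These figures rest on an assumed alpha of 0.05 and an assumed rho; neither is stated, although rho = 0.5 reproduces N = 54.

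The power of 0.451 for a 0.5 SD effect should not be laid at the door of this model choice. It comes mainly from how f = 0.25 translates into a difference in change, and adjustment raises it only to 0.564.

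The largest threat is untouched by either model. Because each clinic runs one group at a time, group is tied to calendar period within clinic, and a period effect passes into both estimates in full.

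**What to change.** Before outcomes are examined by group, amend sections 2.5.9 and 2.8.1 as follows.

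- Primary analysis: one linear model for T2 WAI across all three groups, with two contrasts against TAU, T1 WAI, clinic, and a short fixed list of T1 covariates already collected (for example age, sex, employment, PHQ-9). Name the list in advance.
- Report adjusted mean differences with 95% confidence intervals, and clinic-specific estimates descriptively.
- Keep the 2x2 change-score ANOVAs as a prespecified sensitivity analysis. Commit to reporting and discussing any disagreement, since a stable cohort difference would make the two models diverge.
- State that group is tied to calendar period within each clinic and that neither model removes this confounding.

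The cost is a change of wording and a few degrees of freedom; no new data are needed. The downside to declare is the added assumption that baseline adjustment makes when cohorts are not equivalent.

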Objective measurements include computer and paper-based tests to assess cognitive performance, such as attention span, memory, and reaction times (Corsi Span Test and Color Stroop Test), 6-minute walk test, blood pressure, and 5-minute pulse measurement at rest to assess heart rate variability. Further measurements include clinical assessments of rehabilitation outcomes and medical evaluation of the ability to work (discharge letter) by the physician. The cognitive assessments are not part of routine clinical evaluations; they are specifically implemented for the purposes of this study.

A comprehensive range of outcomes was selected by a multidisciplinary research team to ensure the future provision of optimal support for patients.

The questionnaires are used in all three groups at the beginning baseline (T1; baseline), at the end of rehabilitation (T2), and six months after rehabilitation program (T3). Rehabilitation usually ends after 3 to 4 weeks. The final measurements for the study are taken during the last psychotherapy session in the final week.

Participants with PCS may experience difficulties using the screen and concentrating. To ensure their comfort and reduce any burden, we have made several adjustments available. Participants have the option to take breaks as needed, complete the questionnaires at their own pace, and even continue at a later time if necessary. Additionally, paper versions of the questionnaires can be provided upon request, and participants can also complete them in their rooms if this is necessary. The assessment sessions are expected to take between 70 and 90 minutes per assessment, depending on the individual condition and needs of the patient.

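### The 3x2 ANOVA named for the six-month effect is not specific to six months, and no T3 contrast is named

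*Protocol article*

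**What the plan says.** Section 2.5.7 (Outcomes) sets three assessments: baseline (T1), then "at the end of rehabilitation (T2), and six months after rehabilitation program (T3".

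Section 2.8.1 divides the analysis in two. Change from admission to discharge, for each intervention against TAU, "will be analyzed with 2x2 ANOVAs (2 time points x 2 groups". For follow-up: "The longterm effects after six months will also be analyzed for each intervention group with separate 3x2 ANOVAs (3 time points x 2 groups". No term of the three-time-point ANOVA, no contrast and no follow-up comparison is named.

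Section 2.5.9 (Sample size) describes the planned 2x2 model as a "two-factor ANOVA with one repeated-measures factor and one between-group factor". It also sizes the three-time-point analysis as an ANOVA, again without a contrast: "This means that the sample is also sufficiently large for 2x3 ANOVAs (2 groups x 3 time points; N = 36 required".

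Both hypotheses at the end of the Introduction concern WAI change from pre- to post-treatment. The six-month analysis is therefore secondary.

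**The concern.** With two time points the group-by-time interaction has one degree of freedom and equals the group difference in T2−T1 change, so the 2x2 ANOVA answers the discharge question exactly. With T3 added, the interaction has two degrees of freedom. Its null hypothesis is that the group difference is the same at T1, T2 and T3. A benefit that is present at discharge and gone at six months breaks that null just as a lasting benefit does.

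The group main effect does not fill the gap, because it averages the group difference over all three times, baseline included.

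At stake is the statement about durability. If the interaction is taken as the result for the six-month question, a discharge-only benefit can be reported as a long-term one.

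**Working it through.** **Inputs from the protocol**
- Section 2.5.9: "with 28 individuals in each group", so 56 per pairwise comparison.
- Section 2.5.9: "with a mean effect size of f=0.25 and a power of 0.95, N = 54 patients are required" for the 2x2 comparison of TAU with one intervention.
- Section 2.5.9: "With an estimated drop-out rate of 20%, 100 patients must be recruited". The 84 are defined as having at least admission and discharge data, so T3 numbers may be lower.

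**Assumptions, not in the protocol**
- Alpha 0.05.
- Compound symmetry with SD 1 at each time.
- Correlation rho = 0.5, with 0.3 to 0.7 as the range.
- 22 per group at T3 as a smaller-sample case.

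**Step 1. Reproduce the plan's figure.** For the within-between interaction, lambda = f²·N·m/(1−rho), df1 = (k−1)(m−1) and df2 = (N−k)(m−1). With k = 2, m = 2, f = 0.25, N = 54 and rho = 0.5:

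lambda = 0.0625 × 54 × 2 / 0.5 = 13.5 on 1 and 52 df, power 0.950.

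N = 54 is reproduced, which supports rho = 0.5 as the value behind it.

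**Step 2. What f = 0.25 means in SD units.** With 27 per group, a difference d in change has lambda = (27/2)·d²/[2(1−rho)] = 13.5·d² at rho = 0.5. Setting this to 13.5 gives d = 1.0 SD.

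**Step 3. What the 3x2 interaction responds to.** Let the group differences at T1, T2 and T3 be δ1, δ2, δ3 with mean δ̄. Then lambda = (n/2)·Σ(δj − δ̄)²/(1−rho), on 2 and 2(2n−2) df.

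| Pattern (T1, T2, T3) | Σ(δj − δ̄)² |
|---|---|
| discharge only (0, d, 0) | (2/3)d² |
| six months only (0, 0, d) | (2/3)d² |
| both (0, d, d) | (2/3)d² |

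The three patterns give the same noncentrality, so the test cannot tell them apart. Simulation agrees (20,000 trials per scenario, d = 0.5, n = 28, rho = 0.5): it rejects in 46% (discharge only), 47% (six months only) and 46% (both).

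**Step 4. Rejection rates with zero true difference at T3.** For n = 28, rho = 0.5 and d = 1.0, lambda = 14 × (2/3) × 1 / 0.5 = 18.67. For d = 0.8 it is 11.95 and for d = 0.5 it is 4.67. The simulated rates below agree with the noncentral F calculation to within one percentage point.

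| n per group, rho | d = 0.5 | d = 0.8 | d = 1.0 |
|---|---|---|---|
| 28, 0.3 | 34% | 73% | 91% |
| 28, 0.5 | 46% | 87% | 98% |
| 28, 0.7 | 69% | 98% | 100% |
| 22, 0.5 | 38% | 77% | 93% |

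The group contrast on T3−T1 change rejects in about 5% of trials in every row (0.051, 0.050 and 0.049 for n = 28, rho = 0.5).

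**Step 5. Power given up by using the contrast.** With a true effect at T3 only (n = 28, rho = 0.5), the omnibus test rejects 47% and 87% at 0.5 and 0.8 SD, and the T3−T1 contrast rejects 45% and 84%. With 0.5 SD at both T2 and T3, the figures are 46% and 45%. The loss is two to three percentage points at most in these cases.

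**The case against.** The strongest reply is that section 2.8.1 names a model family and not a decision rule. It never uses the word interaction and never says that a significant one will be read as a six-month effect. A T3−T1 contrast can be taken from the same ANOVA, and an analysis plan not shown may specify it. This stands as a limit: the text does not commit the trial to a misreading. It does not remove the point, because the article assigns the six-month effect to this ANOVA and no omnibus term of it isolates T3. That is a stated method that does not match its stated purpose.

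Two stronger readings are tempting, and neither is supported.
- A reader might infer that the ANOVA is blind to six months. It is not: a T3-only effect is detected as often as a T2-only effect. The test is non-specific.
- A reader might take 46%, 87% and 98% as false-positive rates. They are not: in those scenarios the group profiles do differ and the omnibus null is false. They mislead only if the result is labelled long-term.

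The assumed pattern (a sizeable discharge effect, then exactly zero) is one scenario among many. Section 2.5.9 itself doubts that the add-on will show an effect above d = 0.8, although its f = 0.25 corresponds to 1.0 SD at rho = 0.5. Section 3.1 calls the results preliminary and is cautious about long-term conclusions, which lowers the consequence.

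Loss of patients without T3 is a related but separate matter. A classical repeated-measures ANOVA would drop them, but the article does not say how a missing T3 assessment is handled, and section 2.7.2 plans reminders and a telephone call.

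**Conclusion.** The point holds as a mismatch between a secondary aim and the analysis named for it. A significant 3x2 interaction shows that the group profiles differ somewhere across T1, T2 and T3. It does not show a difference at six months. If the discharge effect on which the trial is sized occurs and then disappears, the interaction will be significant in about 98% of trials at rho = 0.5 (91–100% for rho 0.3 to 0.7). For a discharge effect of 0.5 SD the figure is 46% (34–69%).

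These figures rest on compound symmetry, alpha 0.05, 28 complete patients per group and an assumed rho. The lack of specificity itself depends on none of them. The two formal WAI hypotheses, tested by the 2x2 ANOVAs, are not affected.

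**What to change.** In section 2.8.1:

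1. Name the 1-df group contrast on T3−T1 change, with its estimate and confidence interval, as the test of the six-month effect for each intervention versus TAU.
2. State that the omnibus group-by-time interaction will not be read as evidence of a six-month effect.

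Optionally, estimate the same contrast from a mixed model, so that patients who have not withdrawn and who have T1 and T2 but no T3 still contribute. This must respect the limit in section 2.5.3 on using data from patients who dropped out. A T3 difference adjusted for baseline can be added as a sensitivity analysis. It should not silently replace the change contrast, because in a non-randomized design the two can answer different questions.

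The cost is a sentence or two of analysis text and, from Step 5, a small loss of power. Data, sample size and software (R and SPSS, section 2.7.4) stay the same. The change should be made before six-month data are analysed.
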